### Intervention

Participants will be randomized to 1 of 2 treatment arms: standard immunosuppression reduction alone or immunosuppression reduction in combination with IVIg. The total intended IVIg dose over the 8-wk intervention period will be 2 g/kg, with a tolerance range of 1.8–2.2 g/kg. The recommended dosing schedule is 250 mg/kg weekly for 8 wk, with a 2-wk administration window for flexibility. The first dose of IVIg must be given within 14 d of randomization. Because of potential supply and logistical constraints, the protocol permits IVIg doses to be combined, allowing for up to 2 doses (up to 500 mg/kg) to be administered during a single session.

In both arms, immunosuppression reduction is implemented per current standard of care following a standardized algorithm adapted from the 2024 Transplantation Society guidelines (Table 1).^11^ This typically involves a stepwise reduction in calcineurin inhibitors (CNIs) and antiproliferative agents, or conversion to less potent agents. The protocol provides flexibility for clinicians to alter immunosuppressive therapy according to local standards and clinical judgment. The treatment goal is to achieve a BK viral load <1000 copies/mL, where feasible.

**TABLE 1. T1:** Recommended approach to immunosuppression reduction (adapted from The Second International Consensus Guidelines on the Management of BK Polyomavirus in Kidney Transplantation, 2024^11^)

Strategy 1: Antimetabolite is reduced first
Reduction of the dose of antimetabolite by at least 50%
We suggest further immunosuppression reduction if BKPyV DNAemia does not decrease by 10-fold at 4 wk or does not clear below lower limit of detection as follows:
Discontinuation of the antimetabolite and tapering of corticosteroid dose to 5–10 mg/d of prednisone or equivalent, if applicable
We suggest adding prednisone (or equivalent) 5–10 mg/d for patients who are not on corticosteroids to avoid CNI monotherapy
If further decrease in immunosuppression is necessary, we suggest a stepwise reduction of the CNI dose (tacrolimus trough target 5 ng/mL; cyclosporine trough target 100 ng/mL)
Strategy 2: CNI is reduced first
Reduction of the dose of CNI by 25%–50% in 1 or 2 steps to target trough concentrations of tacrolimus of 3–5 ng/mL and cyclosporine trough concentrations of 75–125 ng/mL)
We suggest further immunosuppression reduction if BKPyV DNAemia does not decrease by 10-fold at 4 wk or does not clear below lower limit of detection as follows:

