### Primary Outcome

The primary outcome is a composite, ordinal outcome assessed at 12 wk (with an acceptable window of 11–13 wk) after randomization (Table 2; Figure 1). Each participant will be assigned to a category on a 5-point ordinal scale, with higher scores indicating worse outcomes:

**TABLE 2. T2:** Primary composite ordinal outcome at 12 wk postrandomization

Primary objective	Outcome measure(s)	Time-point(s)
To compare the efficacy of immunosuppression reduction/ modification strategies, with and without IVIg, on BKPyV infection in kidney and simultaneous kidney-pancreas transplantation recipients	A composite, ordinal outcome defined as: 5: All-cause death or allograft loss (kidney and/or pancreas) or eGFR decline ≥10 mL/min/1.73 m^2^ using the CKD-EPI formula^*a*^ for adults and the Schwartz formula^*a*^ for children 4: Acute rejection (kidney and/or pancreas) or BKV load >1000 copies/mL 3: Large reduction in immunosuppression relative to baseline 2: Moderate reduction in immunosuppression relative to baseline 1: Small to no reduction in immunosuppression relative to baseline Participants will be assigned a category between 1 (best) and 5 (worst).	Week 12

^*a*^ Pancreas graft function loss is defined as kidney-pancreas transplantion recipients’ insulin use is ≥0.5 units/kg/d for 90 consecutive days, or when the recipient’s pancreas graft is removed, and/ or re-registered for a pancreas transplantation.

BKPyV, BK polyomavirus; CKD-EPI, Chronic Kidney Disease Epidemiology Collaboration; eGFR, estimated glomerular filtration rate; IVIg, intravenous immunoglobulin; NB, all timepoints in the above table commence from the date of randomization.

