Reductions in immunosuppression will be defined as minimal, moderate, or large, depending on the degree of immunosuppression reduction required at 12 wk postrandomization (Table 3). The largest reduction in any single immunosuppressive medication (excluding steroid therapy) will be considered for outcome classification. Reductions in antimetabolites will be categorized according to the percentage reduction relative to initial dosing. Reductions in tacrolimus, ciclosporin, and mammalian target of rapamycin (mTOR) inhibitors will be categorized as the reduction in trough target levels at 12 wk relative to initial target trough levels. For patients receiving tacrolimus, ciclosporin, and mTOR inhibitors, their treating clinicians will be asked to specify target levels at randomization and again at 12 wk. Reductions in steroid dosing will not be considered part of the ranked outcome. Substantial variation exists between centers in the use of steroids after transplantation, with some centers adopting steroid-free programs. Therefore, in this cohort, reductions in steroid doses may be unrelated to BKPyV infections.

**TABLE 3. T3:** Classification of immunosuppression reduction by degree of reduction

Immunosuppression medication	Degree of reduction^*a*^	Large	Moderate	Minimal
Antimetabolite	Dose reduction from baseline (%)	≥75%	>25–<75%	≤25%
Ciclosporin (C0 or C2)	Target-level reduction from baseline (%)	≥75%	>25–<75%	≤25%
mTOR-I (trough)				
Tacrolimus (trough, ng/mL)	Baseline trough	Final target trough	Final target trough	Final target trough
	≥8	≤3.9 (or cessation)	4–6.9	≥7
	6–8	≤3.9 (or cessation)	4–5.9	≥6
	4–6	≤2.9 (or cessation)	3–3.9	≥4
	<4	Cessation	≤2.9 (>0)	≥3

^*a*^ The largest reduction in any single immunosuppressive medication (excluding steroid therapy) will be considered for outcome classification.

mTOR, mammalian target of rapamycin.

In addition to dose reductions, conversion from a more potent to a less potent immunosuppressive agent in direct response to BKPyV infection will be classified as a “large” reduction. Conversions performed for other indications, such as drug intolerance, adverse effects, or malignancy, should not be considered a “large” reduction.

Conversions that qualify as “large” immunosuppressive reductions include:

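### Table 3 grades tacrolimus on absolute final targets within wide baseline bands, so its Minimal/Moderate grade does not follow the reduction relative to the initial target

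*Protocol article*

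**What the plan says.** The primary outcome is a five-level ordinal scale at 12 weeks. Participants without a category 4 or 5 event are placed in categories 1 to 3 by how far immunosuppression was reduced. Table 2 defines the best category as "1: Small to no reduction in immunosuppression relative to baseline".

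The text around Table 3 gives the basis for grading. Antimetabolites are graded on percentage dose change. Tacrolimus, ciclosporin and mTOR inhibitors "will be categorized as the reduction in trough target levels at 12 wk relative to initial target trough levels". Clinicians state these targets at randomization and again at 12 weeks.

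Table 3 then uses two kinds of scale:

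- Antimetabolites ("Dose reduction from baseline") and ciclosporin ("Target-level reduction from baseline") are graded in percent: Minimal up to 25%, Moderate above 25% and below 75%, Large from 75%. The mTOR inhibitor cells are blank in the text available; I read them as sharing the ciclosporin line.
- Tacrolimus is graded by the final target in ng/mL within four baseline bands. The top band, 8 or more, has no upper limit.

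One rule combines the drugs: "The largest reduction in any single immunosuppressive medication (excluding steroid therapy) will be considered for outcome classification".

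**The concern.** Categories 1 to 3 are meant to rank how much immunosuppression was given up. With an absolute final target inside a wide band, the tacrolimus grade depends heavily on where in the band the participant started. Two kinds of error follow at the Minimal/Moderate boundary: a trivial or absent change can be marked down to Moderate, and a substantial fall from a high starting target can be marked Minimal.

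Because the highest-graded single drug decides the category, a tacrolimus grade on one scale is compared directly with percentage grades on another. The same classification is reused for the week 48 composite and for the analysis based on the regimen at first qualifying viral load, so any misgrading carries into those results too.

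**Working it through.** **Inputs.** All come from Table 3 and the text around it. The document states no figure of its own to reproduce here.

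| Baseline (ng/mL) | Large | Moderate | Minimal |
|---|---|---|---|
| ≥8 | ≤3.9 or stopped | 4–6.9 | ≥7 |
| 6–8 | ≤3.9 or stopped | 4–5.9 | ≥6 |
| 4–6 | ≤2.9 or stopped | 3–3.9 | ≥4 |
| <4 | stopped | >0 to 2.9 | ≥3 |

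**Formula.** Percentage fall = 100 × (baseline target − final target) / baseline target. Each pair is graded by the tacrolimus rows and by the percentage line used for the other drugs.

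**Small or zero changes**

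| Change | Fall | Tacrolimus rows | Percentage line |
|---|---|---|---|
| 6.5 → 5.9 | 0.6/6.5 = 9% | Moderate | Minimal |
| 4.5 → 3.8 | 0.7/4.5 = 16% | Moderate | Minimal |
| 7 → 5.6 | 1.4/7 = 20% | Moderate | Minimal |
| 2.5 → 2.5 | 0% | Moderate | Minimal |

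The last line is the plainest. The <4 row has no Minimal cell for a participant whose target was already 2.9 or below and was left alone.

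**Larger falls graded Minimal**

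In the ≥8 row the largest fall still graded Minimal, from baseline b, is (b − 7)/b.

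- b = 8: 12.5%
- b = 9: 22.2%
- b = 10: 30.0%
- b = 12: 41.7%

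This passes 25% when b exceeds 7/0.75 = 9.33. The percentage line would grade the last two Moderate. The open upper end is not the only cause: in the bounded 4–6 row, 5.9 → 4 is a 32.2% fall and is also Minimal.

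**When the error reaches the category.** Under the single-drug rule, a wrong Minimal or Moderate tacrolimus grade decides between categories 1 and 2 only if all of these hold:

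- no other non-steroid drug falls by more than 25%;
- no conversion that counts as Large occurs;
- there is no category 4 or 5 event.

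**Do the Large cells conflict with a 25% line?** The smallest falls graded Large, apart from stopping the drug, are 8 → 3.9 (4.1/8 = 51.25%), 6 → 3.9 (2.1/6 = 35%) and 4 → 2.9 (1.1/4 = 27.5%). All exceed 25%, so a 25% rule at the Minimal/Moderate boundary leaves every Large cell as it is.

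**The case against.** Absolute bands look deliberate. The text requires a percentage only for antimetabolites, and a final-target cut-off within a baseline band is one way of making a grade relative to the starting target. A final target of 7 or more also lies above every tacrolimus target that Table 1 names (5, or 3–5 ng/mL), so calling it Minimal is a coherent choice. This stands as a possible reason for the ≥8 row, although the article does not give it. It does not explain how an unchanged target can be a Moderate reduction.

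The affected cells also lie largely off the recommended pathways. Strategy 1 cuts the antimetabolite by at least half, which is already Moderate or Large. Strategy 2, "Reduction of the dose of CNI by 25%–50% in 1 or 2 steps", aims at 3–5 ng/mL, which from a baseline of 8 or more is Moderate or Large once reached. This stands and limits the reach of both errors. It does not remove them, because the Intervention section lets clinicians depart from the algorithm.

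Three stronger readings are tempting, and the document does not support them:

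- **That tacrolimus cuts of 30–53% generally score Minimal.** That range needs baselines of about 10 to 15 ng/mL and a final target still at 7 or above. By contrast, 8 → 5 (37.5%) and 10 → 5 (50%) are Moderate, and 8 → 3.9 (51.25%) is Large.
- **That many participants must start high**, because the Introduction lists greater tacrolimus exposure as a risk factor. That says nothing about the targets set at randomization, and the Secondary Outcomes section expects some regimens to change before then. Any assumed share of the 280 would count people in a baseline band, not people misclassified.
- **That the treatment comparison is biased.** The same rule applies in both arms, and randomization balances baseline targets in expectation. No bias or type I error effect has been shown, and no loss of power has been quantified.

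**Conclusion.** The point holds at the Minimal/Moderate boundary. The tacrolimus grade does not follow the stated basis of reduction relative to the initial target. The firmer half is that falls of 9%, 16% or 0% can score Moderate, against the definition of category 1; this needs no unusually high baseline. The other half, falls above 25% scored Minimal in the ≥8 row, requires a baseline above 9.33 and a final target of at least 7.

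The consequence is non-differential misclassification between categories 1 and 2 of the primary outcome, which blurs what a shift between them means. Its frequency cannot be derived, because the document gives no distribution of baseline or final targets. The conclusion assumes that the targets clinicians state are the values entered into Table 3, as the text says, although the table's column is headed simply as a baseline trough. It is worth correcting but does not invalidate the design.

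**What to change.** Add one line to Table 3 and to the outcome derivation: for tacrolimus, a target fall of 25% or less, including no change, is Minimal, and a fall of more than 25% is at least Moderate. Keep the Large cells and cessation unchanged. Relabel the tacrolimus baseline column as the baseline target trough, to match the text. This alters outcome scoring only and changes no treatment.

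No new data are needed, since both targets are already collected. There are two costs. Some participants will move between categories 1 and 2 relative to the distribution used in the simulations. The Moderate/Large scale for tacrolimus will also still differ from that of the other drugs: a 40% fall would remain Large from 6.5 (to 3.9) and Moderate from 5 (to 3.0), while the other drugs need 75% for Large. If that difference is intended, a sentence giving the reason would help.

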### Secondary Outcomes

The secondary outcomes for this trial were selected in alignment with internationally endorsed transplant outcome standards, including the Standardized Outcomes in Nephrology–Kidney Transplantation^18^ core domains (Table 4). These outcomes will be evaluated at 12-, 24-, and 48-wk postrandomization and encompass indicators of virological response (BKPyV DNAemia, BKPyVAN), graft function (decline in kidney function, allograft loss, biopsy-proven acute rejection), immunological activity (development of de novo donor-specific antibodies), and clinical events (death, hospitalizations, venous thromboembolism events, cancer diagnoses). To account for changes in immunosuppression that may occur before randomization, a sensitivity analysis will evaluate the primary composite ordinal outcome using the immunosuppressive regimen in place at the time the patient first recorded a viral load >5000 copies/ml, rather than the regimen at randomization. This analysis will help determine whether prerandomization modifications influenced the primary outcome.

**TABLE 4. T4:** Secondary outcomes

Secondary objectives	Outcome measure(s)	Time-point(s)
To assess the proportion of participants with a BKPyV viral load reduction between the intervention and control groups	BKPyV final viral load reduction of ≥3 log_10_ or <1000 copies/mL	Week 12
To assess graft function in participants with BKPyV between the intervention and control groups	eGFR decline ≥10 mL/min/1.73 m^2^	Weeks 12, 24, 48
To compare mortality in participants with BKPyV between the intervention and control groups	All-cause death	Weeks 12, 24, 48
To compare graft survival and death-censored graft survival in participants with BKPyV between the intervention and control groups	Graft loss	Weeks 12, 24, 48
To compare the number of acute rejections (cellular- and antibody-mediated) episodes in participants with BKPyV between the intervention and control groups	Acute rejection of kidney and/or pancreas allografts	Weeks 12, 48
To compare the development of de novo donor-specific antibodies in participants with BKPyV between the intervention and control groups	Donor-specific anti-HLA antibody	Weeks 12, 48
To compare the incidence of venous thromboembolism in participants with BKPyV between the intervention and control groups	Venous thromboembolism events	Week 12
To compare the number of hospitalizations because of infection in participants with BKPyV between the intervention and control groups	Hospitalizations because of infection events	All time points
To compare infectious events requiring antimicrobial therapy in participants with BKPyV between the intervention and control groups	Infectious events requiring antimicrobial (antibacterial, antiviral, antifungal, antiprotozoal) therapy	All time points
To compare health-related quality of life in participants with BKPyV between the intervention and control groups	EQ-5D-5L for adults/HUI-3 for children	Baseline, weeks 12, 24, 48
To compare the development of BKPyVAN in participants with BKPyV between the intervention and control groups	BKPyVAN events	Weeks 12, 48
To compare cancer outcomes in participants with BKPyV between the intervention and control groups	Any cancer diagnosis or cancer-related death	Weeks 24, 48
To assess the long-term composite ranked outcome in participants with BKPyV between the intervention and control groups	Composite ordinal outcome (see primary outcome)	Week 48
To assess the cost-effectiveness of IVIg therapy compared with current practice in participants with BKPyV	Incremental cost-effectiveness ratios for the primary outcomes, and quality adjusted life years	Week 48
To assess long-term graft and patient outcomes in participants enrolled from Australia and New Zealand	Linked registry data from the Australia and New Zealand Dialysis and Transplant Registry, including graft function, rejection, graft loss, and death	Posttrial follow-up (via data linkage)
To evaluate the impact of prerandomization immunosuppression changes on the primary composite ordinal outcome using the immunosuppressive regimen in place at the time of first qualifying BKPyV DNAemia (>5000 copies/mL)	Primary composite, ordinal outcome	Weeks 12, 48

BKPyV, BK polyomavirus; BKPyVAN, BK polyomavirus-associated nephropathy; eGFR, estimated glomerular filtration rate; EQ-5D-5L, EuroQol 5-dimension 5-level; HUI-3, health utilities index mark 3; IVIg, intravenous immunoglobulin.

In addition, quality of life will be assessed using validated, age-appropriate instruments, and longer-term effects of the intervention will be captured through a composite ordinal outcome at 48 wk. A trial-based economic evaluation, including healthcare resource utilization and cost-effectiveness of IVIg, will also form part of the secondary analysis.

For participants enrolled in Australia and New Zealand, data linkage with the Australia and New Zealand Dialysis and Transplant Registry will enable extended follow-up beyond 48 wk. Linked outcomes that will include graft function, graft loss, rejection episodes, and death. This longer-term follow-up will facilitate evaluation of the delayed or sustained effects of the intervention that may not be apparent within the initial trial observation period.

### Statistical Analyses

The objective of the primary estimand is to compare the efficacy of immunosuppression reduction with and without IVIg using a composite ordinal outcome at 12 wk postrandomization. This outcome includes 5 levels, ranging from the most favorable (level 1: minimal immunosuppression reduction) to the most severe (level 5: death, allograft loss, or significant decline in kidney function). Anticipated intercurrent events that may occur post-randomization and either preclude or affect the outcome include nonadherence to allocated intervention (because of site procedures, availability, and clinical indication), loss to follow-up or withdrawal, missing histopathology/biopsy results or receipt of a new kidney transplant. For each of these events a “treatment-policy” strategy will be employed where available data will be used up to the time of the event (eg, if a participant is lost to follow-up before 12 wk, then their available data will be used to inform their 12-wk outcome).^19^

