The adaptive trial design includes prespecified interim analyses occurring after 100 participants reach the primary endpoint, and every 60 thereafter. Trial adaptations are based on the posterior probability that the common odds ratio from the primary estimand is <0.9 (ie, the common odds ratio that a participant allocated to the intervention arm will have a better ordinal outcome than a participant allocated to the standard-of-care arm). The trial will stop early for superiority or futility if this posterior probability exceeds 95% or falls below 10%, respectively.

Extensive simulations were conducted to inform key design parameters, including the maximum sample size (n = 280). These simulations evaluated the various scenarios of the treatment effects, the event rates, interim analysis timing, and intercurrent events. For each scenario, 5000 trials were simulated assuming 5% loss to follow-up by 12 wk after randomization. The modeling confirmed that the trial design maintains robust control of type 1 error while achieving adequate statistical power to detect clinically relevant treatment effects across a range of plausible assumptions.

All summary statistics, analyses, and data visualizations will be generated in R version 4.2.2 or later.^21^ A detailed description of the trial estimands, statistical models, decision criteria for adaptations and justification of the trial design by simulation are outlined in **Supplementary File 1** (**SDC**, https://links.lww.com/TXD/A839), with simulation results presented in **Figure S1 and Table S2** (**SDC**, https://links.lww.com/TXD/A839).

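### The primary estimand is labelled treatment-policy but described as using data only up to the intercurrent event; for nonadherence the two contradict each other

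*Protocol article*

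**What the plan says.** The Statistical Analyses section of the protocol article defines the primary estimand on the five-level ordinal outcome. The intercurrent events it anticipates begin with "nonadherence to allocated intervention (because of site procedures, availability, and clinical indication" and continue with "loss to follow-up or withdrawal, missing histopathology/biopsy results or receipt of a new kidney transplant". One rule is then given for all of them: a treatment-policy "strategy will be employed where available data will be used up to the time of the event". The only worked example is attrition: "if a participant is lost to follow-up before 12 wk, then their available data will be used to inform their 12-wk outcome".

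Other sections fix the context:

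- **Primary Outcome:** "The primary outcome is a composite, ordinal outcome assessed at 12 wk (with an acceptable window of 11–13 wk) after randomization".
- **Intervention:** "The total intended IVIg dose over the 8-wk intervention period will be 2 g/kg". The control arm has immunosuppression reduction only.
- **Randomization and Blinding:** all participants are followed for 48 weeks.
- **Statistical Analyses, on design:** stopping depends on the posterior probability that the common odds ratio is below 0.9 (above 95% for superiority, below 10% for futility). The first look comes when 100 participants reach the endpoint, later looks follow every 60, and the maximum is 280. The simulations are said to have varied intercurrent events and were run "assuming 5% loss to follow-up by 12 wk after randomization".
- **Table S1**, in the supplement and not shown, is said to give the estimands and their intercurrent-event strategies.

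**The concern.** A treatment-policy strategy treats the event as irrelevant to which outcome is used: the week-12 category counts whatever happened before. A rule that stops using data at the event is a while-on-treatment type of rule and answers a different question. Two programmers, one following the label and the other the description, could give the same nonadherent participant different primary-outcome categories.

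The direction is not neutral. Only the IVIg arm has a course of infusions to miss or stop, and the course ends before week 12. Entry by viral load requires at least 5000 copies/mL, and category 4 begins above 1000 copies/mL. A participant classified at an early stop would therefore often sit in category 4 even if the virus was controlled by week 12. A death, graft loss or eGFR fall after the stop would not be counted. The resulting odds ratio feeds every superiority and futility decision.

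A second problem is of classification. Loss to follow-up, withdrawal and a missing biopsy leave the outcome unobserved. Treatment-policy needs that outcome and cannot supply it, so these are missing-data problems.

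**Working it through.** **1. Text check, event by event**

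| Listed event | Does a week-12 outcome exist after it? | Effect of stopping at the event |
|---|---|---|
| Nonadherence | Yes, normally (48-week follow-up) | Discards it; contradicts the label |
| Loss to follow-up or withdrawal | No | Nothing to discard; missing data |
| Missing biopsy | The component is unobserved | Nothing to discard; missing data |
| New kidney transplant | Yes, but the preceding graft loss is already category 5 | Little or none |

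The contradiction has practical force for nonadherence.

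**2. The plan's own figure.** 100 + 3 × 60 = 280, so the look schedule agrees with the maximum sample size. The power and type I error behind 280 cannot be reproduced, because the article gives no category probabilities or target odds ratio.

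**3. Illustrative size.** None of these inputs is in the documents:

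- Week-12 control distributions over categories 1–5: A (20, 20, 15, 30, 15%), B (30, 20, 10, 25, 15%), C (10, 15, 15, 40, 20%).
- A fraction f of the IVIg arm is truncated and no control participant is. Nonadherence itself does not change the true week-12 category.
- Harsher freezing: truncated participants are 95% category 4 and 5% category 5.
- Milder freezing: 80% of those who would reach categories 1–3, and half of those who would reach category 5, are recorded in category 4.

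The IVIg distribution comes from multiplying each control cumulative odds by the true odds ratio. The observed IVIg distribution is (1 − f) × true + f × frozen. A proportional-odds model is then fitted to the expected counts (280 participants, 1:1).

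One step by hand, for distribution A, true OR 0.60, f = 10%, harsher freezing:

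- Control probability of category 4 or 5 is 0.45, with odds 0.45/0.55 = 0.818.
- True IVIg odds are 0.60 × 0.818 = 0.491, so the probability is 0.491/1.491 = 0.329.
- Observed IVIg probability is 0.9 × 0.329 + 0.1 × 1 = 0.396, with odds 0.396/0.604 = 0.656.
- The odds ratio at this split becomes 0.656/0.818 = 0.80. Averaged over all four splits, the fitted common odds ratio is 0.72.

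Fitted common odds ratios, range over A–C and both freezing rules:

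| f | True OR 0.60 | True OR 1.00 |
|---|---|---|
| 0% | 0.60 | 1.00 |
| 5% | 0.63–0.67 | 1.03–1.08 |
| 10% | 0.66–0.74 | 1.07–1.16 |
| 20% | 0.73–0.90 | 1.14–1.35 |

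**4. Decision rule.** This uses a normal approximation with a N(0,1) prior, looks at 100/160/220/280, the stated 95% and 10% thresholds, and harsher freezing. At a true OR of 0.60 the probability of success is 64–65% with no truncation, 47–55% at 5%, 31–44% at 10% and 9–24% at 20%. At a true OR of 1.00 it falls from 4.0% to 1.1–2.2% at 10%, so the error does not inflate false success.

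**The case against.** The sentence may be no more than loose condensation. Its only example is loss to follow-up, where data up to the event are simply all the data there are. The treatment-policy label, the fixed 12-week endpoint and the 48-week follow-up all suggest that the authors mean to use week-12 outcomes. Table S1 may word it correctly, and the simulations are said to have covered intercurrent events. This stands as a limit on how confidently one can say what will be done. It does not rescue the sentence, which applies the rule to each listed event, nonadherence among them. A rule stated wrongly is not a detail left to a supplement.

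Some stronger readings are tempting but not supported:

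- **That only IVIg participants would be cut while all controls run to week 12.** Control participants given IVIg are also nonadherent to allocation, and the Introduction notes that IVIg has been used as rescue treatment. The asymmetry is one of degree.
- **That missing values are carried forward, or that a missing biopsy counts as no rejection.** Neither is stated. Available data are said only to inform the 12-week outcome, which is compatible with model-based imputation. The choice of method may be left to the SAP or supplement.
- **That nearly everyone starts above 5000 copies/mL.** Biopsy-confirmed nephropathy is an alternative route of entry, and the qualifying result may be up to 3 weeks old.
- **That the loss of power is a known quantity.** Nonadherence may come late in the course, and the dose tolerance, the administration window and combined doses limit what counts as nonadherence. At 5% truncation the shift is modest.

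**Conclusion.** The contradiction is in the text and should be corrected. For nonadherence, the treatment-policy label and the rule of using data up to the event cannot both hold. Followed literally, the rule would discard week-12 outcomes that will exist, mainly in the IVIg arm, and would pull the common odds ratio toward or past the null. With 10% of that arm truncated, 0.60 would read roughly 0.66–0.74 and 1.00 roughly 1.07–1.16, with lost power and a risk of false futility. These sizes rest on assumed category distributions, assumed freezing patterns and truncation in one arm only, so they show direction and order of magnitude. A reader might infer that the trial will certainly be analysed this way. The article does not establish that, because the intended meaning may be benign and Table S1 has not been seen.

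**What to change.** Replace the single rule with one statement per type of event:

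- **Nonadherence:** the observed week-12 category is used regardless of the event.
- **New kidney transplant:** the graft loss that precedes it is already category 5.
- **Loss to follow-up, withdrawal, missing biopsy:** move these out of the intercurrent-event list and treat them as missing data. Give the method in the SAP or supplement, and keep a known death or graft loss as category 5.

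Make Table S1 and the analysis code agree with this wording before the first interim analysis at 100 participants. If truncation at nonadherence is truly intended, rename the strategy and justify it.

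The cost is a few sentences and a check of the code. No new data are needed, because follow-up already runs past week 12.
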